#### 11.4.5 Baseline parameters and concomitant medications

Baseline parameters, such as age, sex, tumor stage, etc. will be included as confounder into the analyses of secondary objectives, if appropriate. For safety and tolerability analyses, these parameters will not be considered.

#### 11.4.6 Interim analysis

Interim analyses will be performed after every 10 patients from the treatment arm to assess the reoperation complication rate compared to CI of known ratios. If the 95% CI upper limit gets exceeded at any time, the study will be terminated.

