**Table 3. Reoperation cutoff values for study termination.**

| $n^1$ | $CI_{up}^2$ |
|-------|-------------|
| 10    | 4           |
| 20    | 5           |
| 30    | 7           |
| 40    | 8           |
| 50    | 10          |

Number of recruited patients in the treatment arm. Corresponding calculated  $CI_{up}$  number of cases for the complication "reoperation" [1]. If the respective case number exceeds the calculated  $CI_{up}$  number, the study will be terminated.

[figure not shown]

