### 5.2 Study rationale

The concept of combining radiotherapy with ICI is currently investigated in a variety of solid cancers including lung cancer, melanoma and head and neck cancer, as preclinical data has shown some promising synergistic effects [13]–[15]. First clinical results of small patient series support this hypothesis [16]. The safety aspect of this combination has already been documented for liver metastases of melanoma without grade 4 toxicities. Furthermore, ICI has also been combined with chemotherapy, which showed limited toxicity [17]. Yet, little data is known for the combination of CRT with sequential ICI.

Dual checkpoint therapy has been investigated in humans and appears to have additive or synergistic effects [18]–[20]. Usually, dual ICI is given at the same time. However preclinical and experimental data indicate that anti-CTLA-4 deplete regulatory T (Treg) cells and might have a priming effect for cytotoxic T cells following anti-PD-1 treatment to counterattack T cell exhaustion. Thus, the sequential blockade of the CTLA-4 and PD-1 might have an additional advantage to simultaneously inhibition.

Most recent it was shown that immunomodulating therapy applied before surgical resection are highly beneficial, which increase the recurrent-free survival (RFS) [21]–[25]. This finding suggests that systemic immune stimulation appear to purge occult micrometastases. Thus, the highest biological effects of immunotherapy might be in the early phase to tumor treatment, which focuses on the enhancement of cure rates. This provides the rationale to combine ICI with currently applied standard neoadjuvant therapies in solid tumors.

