## 6 STUDY OBJECTIVES

### 6.1 Primary objective

- Safety, tolerability and feasibility of sequential neoadjuvant ipilimumab and nivolumab in combination with standard neoadjuvant CRT, following surgical resection, assessed by the latest “Clavien-Dindo Classification of surgical complications” [26] (see section 9.1.2 ) and Common Terminology Criteria of Adverse Events (CTCAE) [27] (see section 9.4 ).

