#### Replacement policy

Patients who discontinue the clinical trial before receiving the first cycle of treatment will be replaced. All other drop-outs will be included in the sample size.

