### 7.1.7 Premature termination of the study

The sponsor has the right to close this study at any time. The IEC and the competent regulatory authority must be informed within 15 days of early termination.

The trial or single dose steps will be terminated prematurely in the following cases:

- If adverse events occur which are so serious that the risk-benefit ratio is not acceptable.
- If the number of dropouts is so high that proper completion of the trial cannot realistically be expected.

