## 8.3 Surgery

Patients will be operated about 10-12 weeks post CRT. Surgical options included standard total mesorectal excision (TME) or extended TME (*i.e.* TME with adjacent visceral resection) with or without sphincter preservation (abdominoperineal excision; APE) according to a standardized technique [34][3]. Patients will receive either a minimal invasive (laparoscopic, laparoscopic-assisted or robotic) or an open approach, depending on the perioperative circumstances (*i.e.* body constitution and cardiopulmonary fitness of the patient) and the surgeon's choice and expertise.

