### 11.4 Statistical analysis plan (SAP)

#### 11.4.1 Missing, unused and spurious data

In general, every effort shall be made by site staff to avoid the occurrence of missing data. However, in case data is not recorded, this must be clearly stated in the eCRF. The statistical analysis will also report the frequency of missing values.

Patients with missing data for a specific side effect will be excluded from the evaluation of this side effect. Missing data for secondary objectives will be imputed with values estimated by the predictive mean matching method using R-package “mice” (version 2.30), if appropriate.

[figure not shown]

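### Table 3 applies its reoperation stopping limits to recruited patients, although the limits assume that every counted patient has been operated

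*Protocol*

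**What the plan says.** The synopsis (Statistical methodology), Table 3 and section 11.4.6 set one scheduled numeric rule: "Interim analyses will be performed after every 10 patients from the treatment arm to assess the reoperation complication rate". The study ends if the count exceeds 4, 5, 7, 8 or 10 at n = 10, 20, 30, 40 or 50. The body text speaks only of patients of, from or in the treatment arm or group. The Table 3 footnote alone says what n is: "Number of recruited patients in the treatment arm".

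Four other places bear on who is counted and when:

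- Section 8.3: "Patients will be operated about 10-12 weeks post CRT". With five weeks of CRT, this is Week 15-17 in the visit schedule (Table 4).
- Section 7.1.6 replaces only patients who leave before the first cycle, and adds: "All other drop-outs will be included in the sample size".
- Section 11.4.1: "Patients with missing data for a specific side effect will be excluded from the evaluation of this side effect".
- Section 11.4.6 also says that crossing the limit ends the study whenever it happens, while the synopsis and the termination criteria speak of an assessment after every 10 patients.

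**The concern.** A patient who has not had the resection cannot be reoperated. If n counts recruited patients, those still waiting for surgery and those who never reach it enlarge n without being able to contribute an event. The limit is then set for more patients than are at risk, so a given true reoperation rate is less likely to cross it. The error runs in the unsafe direction: anything that delays or prevents surgery, including toxicity of the study drugs, makes the only numeric termination rule harder to trigger. Whether this happens depends on which of the passages above is followed, and a termination rule should not depend on that.

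**Working it through.** **Inputs.** Reference reoperation rate 7% (Table 1). Looks at n = 10 to 50 and limits 4/5/7/8/10 (Table 3). Exact binomial interval with round half up (11.4.7). Surgery at Week 15-17 (8.3, Table 4). Treatment arm of 50; first visits from 1Q 2020 to 2Q 2022, that is 24-30 months (synopsis). Even accrual is an assumption. So are the true rates of 14% and 21% (double and triple the reference) and the shares never operated.

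**Step 1: reproduce Table 3.** Take x = round-half-up(0.07 × n). The upper limit U is the 0.975 quantile of Beta(x + 1, n − x), and the cutoff is round-half-up(n × U).

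| n | x | n × U | Cutoff | Table 3 |
|---|---|---|---|---|
| 10 | 1 | 4.45 | 4 | 4 |
| 20 | 1 | 4.97 | 5 | 5 |
| 30 | 2 | 6.62 | 7 | 7 |
| 40 | 3 | 8.15 | 8 | 8 |
| 50 | 4 | 9.62 | 10 | 10 |

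The match is exact. The calculation treats all n patients as binomial trials, so all n must be at risk.

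**Step 2: patients not yet operated at a look timed by recruitment.** With 4.345 weeks per month:

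- 50 / (24 × 4.345) × 17 weeks = 8.2
- 50 / (30 × 4.345) × 15 weeks = 5.8

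About 6-8 are therefore waiting, and the numbers operated at the five looks are 2-4, 12-14, 22-24, 32-34 and 42-44.

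**Step 3: look 1.** Stopping needs at least 5 reoperations, and only 2-4 patients have been operated. The probability of stopping is 0 at any rate. With all 10 operated it would be 4.0% at a true 21%.

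**Step 4: cumulative stopping over five looks.** At each look the new reoperations are binomial in the newly operated patients. The trial stops when the running count exceeds the limit, and the first-crossing probabilities are summed exactly.

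| Reading | True 7% | True 14% | True 21% |
|---|---|---|---|
| All n operated at every look | 0.35% | 14.0% | 57% |
| 6-8 waiting at looks 1-4, all 50 operated at look 5 | about 0.1% | 8.9-9.5% | about 50% |
| 6-8 waiting at every look | 0.04-0.07% | 4.1-5.8% | 30-37% |

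**Step 5: patients never operated but kept in n.** Ignoring the lag, a share q never operated changes the event probability per counted patient from p to p(1 − q). At p = 14% this gives 13.3%, 12.6% and 11.2% for q = 5%, 10% and 20%.

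| Never operated (assumed) | True 14% | True 21% |
|---|---|---|
| 0% | 14.0% | 57% |
| 5% | 11.1% | 50% |
| 10% | 8.6% | 43% |
| 20% | 4.8% | 29% |

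**The case against.** **The text may not mean this.** The point rests on one word in a footnote. The body text does not say recruited, and 11.4.1 can be read as dropping patients without a reoperation outcome. This stands: the documents do not show that the diluted count will be used. But the footnote is the only place that defines n, and 7.1.6 points the same way.

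**The 4-6% figure is the least favourable reading.** A reader might take it as the size of the defect. The documents do not support that. The synopsis also compares case numbers after the end of the study; if the n = 50 comparison uses all 50 operated, the figure is about 9%. If crossing at whatever moment is read as a running check against the current limit until all 50 are operated, the rule stops 15.3-18.5% at a true 14%, above the 14.0% of the fully operated case. This too stands, and it shows how far the rule's behaviour depends on interpretation.

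**The effect is modest beside the rule's own leniency.** With everyone operated, a doubled rate still stops only 14.0% of trials. That is true, and redefining n does not change it.

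**There is another safeguard.** Section 7.1.7 also allows termination when drop-outs are too many, which may catch patients whose surgery is prevented. It carries no number.

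**A stronger reading on toxicity.** CTCAE toxicity is part of the primary objective (6.1), and section 5.2 says: "Yet, little data is known for the combination of CRT with sequential ICI". A reader might infer that the trial has no stop for drug toxicity, or that lacking a numeric CTCAE limit is an error. The documents do not support this. Section 7.1.7 ends the trial "If adverse events occur which are so serious that the risk-benefit ratio is not acceptable", and patient-level discontinuation and prompt SAE reporting apply. No acceptable toxicity rate is stated from which a limit could be derived. With an assumed 20% ceiling and the protocol's own method, six of ten patients with an event would pass look 1, and at a true 40% only 5.5% of trials would pause there. A numeric boundary is a design choice.

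**Conclusion.** The concern holds for the denominator of the reoperation rule. The Table 3 limits are computed correctly, but for patients at risk, while the footnote attaches them to recruited patients. On that wording and with recruitment-timed looks, the first look cannot stop the trial. At a doubled reoperation rate the whole rule stops about 4-6% or about 9% of trials, depending on the last look, instead of 14.0%; at a tripled rate 30-37% or about 50%, instead of 57%. These figures rest on even accrual over 24-30 months: faster accrual widens the gap and slower accrual narrows it. The never-operated figures rest on assumed shares; the loss is small at 5% and clear at 20%. Because 11.4.1 and the wording in 11.4.6 allow other readings, the finding is an unsettled termination rule that can be too lenient, not one shown to be so. It should be corrected, because it concerns participant safety and the change is small.

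**What to change.** In the Table 3 footnote, the synopsis, 11.4.6 and the termination criteria, define n as treatment-arm patients who have been operated and have completed postoperative follow-up to the end-of-study visit. Hold a look after every 10 such patients and leave the limits at 4/5/7/8/10. Add that a reoperation count already above the limit for the next look stops the trial at once, whether or not those patients have reached that visit. This gives the wording in 11.4.6 about crossing at any moment a definite meaning.

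**Cost.** The wording changes in four places. Looks come later: at the assumed accrual, 50 / (30 × 4.345) × 20 = 7.7 to 50 / (24 × 4.345) × 20 = 9.6 further treatment-arm patients are recruited in the 20 weeks to the end-of-study visit. The immediate-stop sentence limits that delay. If only 40-49 patients become evaluable, the n = 50 look is not reached, and looks at 10-40 stop 12.1% at a true 14% and 50% at 21%. Where 5% are never operated, the gain at 14% is therefore only from 11.1% to 12.1%.

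**Secondary suggestion, not a correction of an error.** The sponsor could add to 7.1.7 a pause of enrolment for review after any grade 5 event with a reasonable causal relationship to study drug. It should use the definition in 9.6, because the algorithm in 9.5 requires the event to subside on withdrawal, which a death cannot do. At an assumed treatment-related death rate of 0.5%, 1% or 2%, such a pause would occur at least once within 50 patients in 1 − 0.995^50 = 22%, 1 − 0.99^50 = 39% or 1 − 0.98^50 = 64% of trials.

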##### **Criteria for the termination of the trial**

The study will be terminated if the frequency of the complication "reoperation" will exceed the calculated 95% CI upper limit (Table 3). This will be assessed after every 10 patients in the treatment group.

[figure not shown]

#### 11.4.7 Software program

All statistical analyses will be computed with R version 3.6.1 [43]. The R-package “binom 3.6.0” using the “*binom.test*” function (exact binomial test). Rounding to the concrete case numbers was performed with an own rounding function implementing the “round half up” method, not the round to even method usually used from the R round-function.

[figure not shown]

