**Table 1. Incidence of know complications for neoadjuvant CRT following surgical resection.**

| Complications (n=128)          | Percentage (%) | Citation |
|--------------------------------|----------------|----------|
| Any postoperative complication | 39             | [1]      |
| Any surgical complication      | 23             | [1]      |
| Reoperation                    | 7              | [1]      |

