### Statistical methodology

Interim analyses will be performed after every 10 patients from the treatment arm: Reoperation numbers will be determined and the 95% CI compared to historically known and published ratios [1].

95% CI (Exact binomial test) for complication percentages between 5% and 40% in 2.5 steps and expected case numbers are calculated for n=30 (control group) and n=50 (treatment group) patients (Table 2).

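### Table 3 rounds the 95% upper limits to the nearest case, so at 20, 30 and 50 patients a reoperation count above the calculated limit does not stop the study

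*Protocol*

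**What the plan says.** The interim rule appears in two forms.

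- **As a limit.** Section 11.4.6 says: "If the 95% CI upper limit gets exceeded at any time, the study will be terminated". The termination criteria under it repeat the rule for the frequency of reoperation, which must not go beyond the limit: "will exceed the calculated 95% CI upper limit (Table 3").
- **As a count.** The synopsis text before Table 3 stops the study when observed cases are above the border case numbers. The Table 3 footnote likewise requires the case number to exceed the tabulated "number, the study will be terminated". The cutoffs are 4, 5, 7, 8 and 10 at 10, 20, 30, 40 and 50 treatment-arm patients.

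Section 11.4.7 links the two. The limits come from R, "using the “*binom.test*” function (exact binomial test"), and "Rounding to the concrete case numbers was performed with an own rounding function implementing the" half-up method. The same construction gives Table 2, where the synopsis calls the treatment unsafe for a complication if treatment-arm cases are above the upper border. The unrounded limits are not printed anywhere.

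**The concern.** An upper limit of, say, 6.62 cases is exceeded by 7 cases. If 6.62 is printed as 7 and the printed number must itself be exceeded, 7 cases no longer count. For whole-number counts, 'above U' means the same as 'above U rounded down'. Nearest-integer rounding therefore agrees with the limit when it rounds down and is one case more lenient when it rounds up. At this step it can never be stricter.

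Reoperation is the only termination criterion in the protocol with a number attached; those in section 7.1.7 are qualitative. If its cutoff is labelled a 95% upper limit but lies above that limit at three of five looks, the rule has less chance of stopping than its label implies. The Table 2 borders, which decide the primary endpoint, share the feature.

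**Working it through.** **Inputs.** Reference reoperation rate 7% (Table 1). Exact binomial 95% interval (synopsis, Statistical methodology; section 11.4.7). Looks at n = 10, 20, 30, 40 and 50 (Table 3). Rounding as in section 11.4.7.

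**Step 1: reproduce Table 3.** Expected cases x = 0.07 × n, rounded half up. Upper limit U = 97.5th percentile of Beta(x + 1, n − x). Limit in cases = n × U.

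| n | 0.07n | x | U | n × U | nearest integer | Table 3 | rounded down |
|---|---|---|---|---|---|---|---|
| 10 | 0.7 | 1 | 44.50% | 4.45 | 4 | 4 | 4 |
| 20 | 1.4 | 1 | 24.87% | 4.97 | 5 | 5 | 4 |
| 30 | 2.1 | 2 | 22.07% | 6.62 | 7 | 7 | 6 |
| 40 | 2.8 | 3 | 20.39% | 8.15 | 8 | 8 | 8 |
| 50 | 3.5 | 4 | 19.23% | 9.62 | 10 | 10 | 9 |

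All five cutoffs are reproduced. The same steps reproduce every count and border in Table 2 for both arms.

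**Step 2: compare the printed cutoffs with the limits.**

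- n = 20: 5/20 = 25.0% against 24.87%, above the limit by about 0.03 of a case.
- n = 30: 7/30 = 23.3% against 22.07%, above by 0.38 of a case.
- n = 50: 10/50 = 20.0% against 19.23%, above by 0.38 of a case.
- n = 10 and n = 40: the limit rounds down, so the printed cutoff agrees with it.

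**Step 3: Table 2, treatment arm (n = 50).** Six of 15 rows round up:

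| Row | n × U | Printed | Rounded down |
|---|---|---|---|
| 7.5% | 9.62 | 10 | 9 |
| 10% | 10.91 | 11 | 10 |
| 15% | 14.56 | 15 | 14 |
| 17.5% | 15.72 | 16 | 15 |
| 20% | 16.86 | 17 | 16 |
| 22.5% | 17.98 | 18 | 17 |

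The rows nearest two of the Table 1 references are among them: 7.5% for reoperation (7%) and, by only 0.02 of a case, 22.5% for surgical complications (23%). The 40% row, nearest to 39% for any postoperative complication, rounds down (27.41 to 27) and is unaffected.

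**Step 4: effect on stopping.** Exact binomial recursion in cohorts of 10, removing at each look the sequences that have already stopped. Printed cutoffs 4, 5, 7, 8, 10 stop at ≥5, ≥6, ≥8, ≥9, ≥11 cases. Rounded-down cutoffs 4, 4, 6, 8, 9 stop at ≥5, ≥5, ≥7, ≥9, ≥10.

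| True reoperation rate | Looks | Printed counts | Unrounded limit |
|---|---|---|---|
| 7% | 10–50 | 0.35% | 1.3% |
| 14% | 10–50 | 14.0% | 23.9% |
| 14% | 10–40 | 12.1% | 19.5% |
| 20% | 10–50 | 50.5% | 63.7% |
| 20% | 10–40 | 44.1% | 53.3% |

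**The case against.** - **The rule can be applied as printed.** The termination criteria cite Table 3, the synopsis and the table footnote define the trigger in counts, and section 11.4.7 discloses the rounding. This stands. A reader might infer that the text orders termination at 5/20, 7/30 and 10/50 while the table orders continuation. The documents do not support so flat a contradiction, because the criterion points to the table. What remains is a mismatch: the cutoffs bear the name of a 95% upper limit, and section 11.4.6 states that limit without reference to the table, yet three cutoffs lie above it.
- **Half-up rounding is not the cause.** A reader of section 11.4.7 might blame the custom function. No limit falls on .5, so R's default rounding gives the same table. The cause is rounding an upper limit to nearest when the rule is 'exceeds'.
- **Direction.** An earlier rounding, of the expected count, can move the limit either way. Putting 7% × n unrounded into the same formula gives 5.54 at n = 20, above the printed 5, and 8.95 at n = 50, below the printed 10. But the plan's function needs whole counts, so this is not the plan's method. The one-sided direction holds for the last rounding step, given the plan's own limits.
- **Size.** At n = 50 all treatment-arm patients are recruited, so that look cannot spare later patients in the arm. This stands; the 10–40 figures are the fairer measure of protection during recruitment.
- **Control arm.** Twelve of its 15 upper borders in Table 2 also round up. A reader might count these as missed harm. They are not a harm boundary: section 11.4.2 uses that arm to check the expected rates.
- **The rule stays weak.** Even with the unrounded limits, a doubled rate goes undetected in about 76% of trials (100 − 23.9). This is true, and it is a separate matter.

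**Conclusion.** The point holds as a mismatch between the stated limit and the tabulated cutoffs. At three of five looks, and in six of 15 treatment-arm rows of Table 2, the printed number lies above the 95% limit that it is said to represent. The excess allowed is one case in each instance. At a true 14% this lowers the chance of stopping from 23.9% to 14.0%, or from 19.5% to 12.1% over looks 10–40. At the 7% reference it lowers false stopping from 1.3% to 0.35%.

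The calculation takes the plan's interval method as given. It also assumes independent patients with a constant rate, and reoperation status known for all n patients at each look. It should be corrected because it affects the only numerical stopping rule and the primary-endpoint borders, but it does not make the rule unworkable.

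**What to change.** Reconcile the synopsis text around Tables 2 and 3 with sections 11.4.6 and 11.4.7 so that all state the same criterion. Which one applies is for the sponsor to decide.

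- **If the 95% limit is the intended criterion:** in section 11.4.7, round upper limits down, or compare the observed percentage with the unrounded limit. On the plan's own method Table 3 then reads 4, 4, 6, 8, 9, and the six Table 2 treatment-arm borders (7.5, 10, 15, 17.5, 20 and 22.5% rows) become 9, 10, 14, 15, 16, 17. The percent-change column in those rows needs updating too.
- **If the printed counts are intended:** say in section 11.4.6 that the count is the criterion and that it lies above the 95% limit at n = 20, 30 and 50, and give the resulting stopping probabilities.

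The first option costs two re-issued tables and one changed sentence, with about 1 percentage point more false stopping at a true 7% (0.35% to 1.3%). The second costs a few sentences.
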